#### **3.3 SAMPLE SIZE**

The sample size of each hypothesis is calculated by using the G\* power analysis. Given that this is a novel study and there is no reference from previous study, sample size was calculated using ANOVA repeated measures, within-between interaction with Cohen-f effect size at 0.25 for a medium effect, alpha error at 0.05 and 80% power. Result showed that a total of 34 participants will be needed. By adding 10% dropout rate, the required sample size became 38 participants.

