- g. An independent Therapist C who is not assessing or treating the participants will be given an equal numbers of random allocation cards with designated alphabet of “C” (Control group) and “I” (Intervention group). Therapist C will then insert each allocation card into an opaque envelope. Each envelope that contains a random allocation card with either “C” or “I” notation will be sealed and enclosed with glue. Therapist C will give the corresponding envelope to each enrolled participant after he/she has completed all the baseline assessment. The selected envelope will be opened by the participant immediately in the presence of Therapist C. Therapist C subsequently records the allocated group of either “C” or “I” for the respective participant on the excel sheet prepared by the researcher. The information regarding participant group allocation will only be known by the researcher and Therapist C. Both the Therapist A and Therapist B will not be informed about the group allocation of each participant.

- h. Both participants from the control and intervention groups will be receiving conventional therapy that includes splinting, scar management, edema management, physical agent modalities, e.g. hot/cold pack, ultrasound, Transcutaneous Electrical Nerve Stimulation (T.E.N.S.), Neuromuscular Electrical Stimulation (N.M.E.S.), passive/active stretching, joint mobilization, strengthening exercises, and hand function training.
- i. Each participant from both the control and intervention groups will receive two conventional therapy sessions daily that include an occupational therapy session and a physiotherapy session on a 5-day/week routine basis. Each occupational therapy and physiotherapy session will last for 90 minutes respectively. In addition to the conventional therapy, the intervention group will receive a 60-minutes HAL-SJ robotic therapy session conducted by the researcher daily on a 5-day/week routine basis within two hours after the conventional therapy sessions.
- j. All participants will be receiving this 5-day/week therapy sessions for a duration of four weeks. Reassessment of therapeutic outcome for both control and intervention groups will be conducted by the Therapist A upon completion of the therapy program after 4 weeks.

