### **3.8 STATISTICAL ANALYSIS**

All data will be analysed using the IBM® SPSS® Statistics version 28. The study will use both descriptive and inferential statistics to analyse the data. Descriptive analysis for categorical data including gender, marital status, hand dominance, types of medical management and intervention, type of wrist fractures, educational level, employment status, and type of SOCSO compensation scheme will be expressed in frequency, percentage or/and proportion. Descriptive statistics for continuous data including age, DASH, pain, grip and pinch strength, wrist and finger ROM, hand dexterity, and work readiness scores will be expressed in mean, standard deviation, maximum, and minimum if the data is normally distributed or in median and inter-quartile range if the data is not normally distributed. The Shapiro-Wilks test will be used to test the normality of the continuous data.

The statistical analysis for each hypothesis will be tested using mixed model ANOVA by evaluating the mean differences in treatment outcomes between the groups at baseline and after 4 weeks of intervention.

Intention-to-treat (ITT) analysis will be used to analyze the difference between groups. ITT analysis, which aims to minimize bias and maintain random allocation of study participants (Gupta 2011), is suitable to be used when there are shedding participants. Its key idea is to analyse the group to which the participant belongs in that initial allocation, regardless of whether they completed the study or received the intended intervention.

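### ITT is promised regardless of completion, but the only reassessment is tied to completing therapy and the two-time-point ANOVA omits anyone without week 4, so by default the analysis is not ITT as promised

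*Combined protocol and SAP*

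**What the plan says.** - **Analysis principle (3.8).** "Intention-to-treat (ITT) analysis will be used to analyze the difference between groups". The section presents ITT as suited to trials that lose participants, and gives its key idea as being to "analyse the group to which the participant belongs in that initial allocation, regardless of whether they completed the study or received the intended intervention".
- **Model (3.8).** Each hypothesis is "tested using mixed model ANOVA by evaluating the mean differences in treatment outcomes between the groups at baseline and after 4 weeks of intervention". The software is SPSS 28; no SPSS procedure is named.
- **Outcome assessment (3.5(j)).** Reassessment in both groups "will be conducted by the Therapist A upon completion of the therapy program after 4 weeks". The Appendix J record sheets have an initial assessment and one reassessment, and no other visit.
- **Withdrawal (3.7).** Participants may leave at any stage. No later outcome visit is described for them.
- **Sample size (3.3).** The "sample size was calculated using ANOVA repeated measures, within-between interaction". The inputs are f = 0.25, alpha 0.05 and 80% power, giving 34. "By adding 10% dropout rate, the required sample size became 38 participants".
- **Missing data.** The only visible rule is the DASH item rule in Appendices C to E: no score if more than 3 items are missing. Nothing covers a missing week-4 assessment.

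**The concern.** An ITT comparison needs an outcome, or a stated way of handling its absence, for everyone who was randomised. The plan anticipates losses and promises to keep those participants in the comparison, but provides neither a visit that would capture their outcome nor an analysis that would use their record. Someone who stops therapy in week 2 has a baseline value, no scheduled reassessment, and no change score.

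At stake is whether the comparison remains the randomised one. If those without a week-4 value differ between arms in baseline severity or in the course they would have followed, the contrast is biased, and the report would still carry the ITT label. Only the intervention arm has an additional 60-minute daily session (3.5(i)) and the minor skin and soreness effects listed in 3.6.1. Unequal loss is therefore possible, although the documents give no data on it.

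**Working it through.** **1. Reproduce the plan's sample size.** Inputs from 3.3: f = 0.25, alpha 0.05, power 80%. Inputs from 3.5 and 3.8: 2 groups, m = 2 time points. The baseline to week-4 correlation rho is not given; 0.5 is assumed.

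For the within-between interaction, lambda = f² × N × m / (1 − rho), with 1 and N − 2 degrees of freedom.

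- N = 34: lambda = 0.0625 × 34 × 2 / 0.5 = 8.5; power 0.807.
- N = 32: lambda = 8.0; power 0.781.

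The smallest even N reaching 0.80 is 34, as stated. Other correlations would give 66 (rho 0), 46 (rho 0.3) or 22 (rho 0.7). For dropout, 34 / 0.90 = 37.8 and 34 × 1.10 = 37.4; both round up to 38. So 3.3 reproduces under a two-time-point repeated-measures ANOVA with rho = 0.5.

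**2. What that model does with a missing week 4.** With two groups and two time points, the interaction test is a two-sample comparison of change (week 4 minus baseline). Without week 4 there is no change. In a simulated data set of 38 participants with 4 missing week-4 values, the ANOVA used 34 people, while a likelihood mixed model kept all 38 records.

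**3. How many might be affected.** 38 − 34 = 4 expected losses under the plan's own 10%. With outcomes on all 38, lambda = 9.5 and power is 0.851, against 0.807 with 34.

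**4. Illustration of bias (assumed figures).** Suppose the 2 of 19 with the worst baseline scores in one arm have no week 4, and nobody is lost in the other. Scores are taken as normal, higher being worse as on the DASH, with SD 1 at both times and no true difference in change.

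- Fraction lost: q = 2/19 = 0.105; normal cut-point z = 1.252; density at z = 0.182.
- Baseline mean of those remaining: −0.182 / (1 − 0.105) = −0.204 SD.
- Their expected week-4 mean is shifted by rho × (−0.204), so their mean change is shifted by (rho − 1) × (−0.204).

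| rho | Shift in change contrast | Detectable difference, N = 34, 80% power | Ratio |
|---|---|---|---|
| 0.5 | 0.5 × 0.204 = 0.10 SD | 0.99 SD | 0.10 |
| 0.3 | 0.7 × 0.204 = 0.14 SD | 1.17 SD | 0.12 |

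The second detectable difference is 0.99 times the SD of change, √(2 × 0.7) = 1.18. The shift goes against the arm with the losses, because the participants with most room to improve are missing. In simulation at rho = 0.5 the change-score bias was 0.097 SD, and adjusting for baseline reduced it to 0.000.

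**5. A different mechanism.** If the 2 lost participants would have changed 1 to 2 SD less than the rest of their arm, that arm's mean change is off by 2/19 × 1 = 0.11 to 2/19 × 2 = 0.21 SD. This depends on outcomes nobody observed, so baseline adjustment does not in general remove it.

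**6. When it vanishes.** If both arms lose the same fraction with the same profile, both mean changes shift equally and the contrast is unaffected.

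**The case against.** The strongest reply is that the plan nowhere says cases are deleted. The name of the model in 3.8 could mean a linear mixed model, and SPSS 28 is cited without a procedure. That is a possible reading, but the model used in 3.3 favours repeated-measures ANOVA. Even a linear mixed model would have no week-4 outcome for people who left, and would rest on a missing-at-random assumption that the plan does not state.

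Second, 3.5(j) can be read as a fixed time point, since it ends by naming 4 weeks. A participant who misses sessions but attends reassessment is analysed as allocated under either reading. This stands, and it means that incomplete therapy must not be equated with a missing outcome. But no visible section extends the visit to people who have stopped. The flow chart (3.9) and the Appendix K forms are not in the text available, so the absence can be asserted only for what is visible.

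Three stronger inferences are tempting and unsupported:

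- **That the 10% inflation confirms that dropouts are discarded.** Allowing for dropout is routine and compatible with ITT, because missing outcomes cost information under any analysis. The figure of 4 is only an expectation.
- **That good recoverers must leave on returning to work.** Being on medical leave and not back at work is an entry criterion (3.4.1(a)); nothing makes it a condition for staying.
- **That dropout will differ between arms.** The documents give no data, and 3.6.1 calls the device effects minor.

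Finally, the illustrated shift is modest beside sampling error. With 17 against 19 analysed, the standard error is 0.33 SD at rho 0.5 (√(1/17 + 1/19)) and 0.40 SD at rho 0.3 (1.18 times as large), so the shift is about 0.30 to 0.36 standard errors. That is fair, and it is a reason not to overstate the point.

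**Conclusion.** The concern holds in this form: as written, the promised ITT analysis becomes by default an analysis of participants with both assessments. This rests on reading 3.8 together with 3.3 as a repeated-measures ANOVA, and on no visible text recalling people who stop therapy or handling a missing week 4. It does not show that the plan instructs deletion, or that the result will be biased.

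The size depends on the pattern of loss. It is about 0.10 to 0.14 SD for one-sided, baseline-driven loss of 2 in 19, 0.11 to 0.21 SD if the lost participants would have changed 1 to 2 SD less than the others, and nil if losses are alike in both arms. The correlation and the loss patterns are assumptions. The sample size itself is not in error. The plan should be changed because the correction is cheap and the ITT claim otherwise has no mechanism behind it.

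**What to change.** 1. **Section 3.5(j).** State that every randomised participant is reassessed 4 weeks after randomisation, whatever their therapy attendance, unless consent is withdrawn. This is the only step that recovers outcomes which would otherwise be unobserved.
2. **Section 3.8.** Replace the ANOVA with a likelihood mixed model on all randomised participants: SPSS MIXED, REML, unstructured covariance for the two time points, common baseline mean across arms. State the missing-at-random assumption, and that the model removes baseline-driven bias but not bias from unobserved outcomes.
3. **Section 3.8.** Add a sensitivity analysis that varies the missing week-4 changes in both directions, worse and better, and separately by arm.

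In 3.3, also state the assumed correlation and the number of measurements.

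**Cost.** Wording changes, a few recall visits (about 4 if the 10% assumption holds) and a little more analysis. DASH and LASER could be collected remotely from those who will not attend. The VAS line must be marked by the participant on paper, and motion, strength and dexterity need attendance. N stays at 38.

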### 3.9 RESEARCH FLOW CHART

[figure not shown]

### 3.10 GANTT CHART

|                                        | 2020 |     |     |     |     |     |     |     |     |     |     |     |
|----------------------------------------|------|-----|-----|-----|-----|-----|-----|-----|-----|-----|-----|-----|
|                                        | Jan  | Feb | Mar | Apr | May | Jun | Jul | Aug | Sep | Oct | Nov | Dec |
| Proposal Preparation                   | √    | √   |     |     |     |     |     |     |     |     |     |     |
| Proposal Presentation                  | √    | √   |     |     |     |     |     |     |     |     |     |     |
| Application of Ethics Approval         |      |     |     |     |     |     |     |     |     |     | √   | √   |
| Participants Recruitment and Selection |      |     |     |     |     |     |     |     |     |     |     |     |
| Intervention Implementation            |      |     |     |     |     |     |     |     |     |     |     |     |
| Data Collection                        |      |     |     |     |     |     |     |     |     |     |     |     |
| Data Analysis                          |      |     |     |     |     |     |     |     |     |     |     |     |
| Chapter 1                              | √    | √   | √   | √   | √   | √   | √   | √   | √   | √   | √   | √   |
| Chapter 2                              | √    | √   | √   | √   | √   | √   | √   | √   | √   | √   | √   | √   |
| Chapter 3                              |      |     |     |     |     |     | √   | √   | √   | √   | √   | √   |
| Chapter 4                              |      |     |     |     |     |     |     |     |     |     |     |     |
| Chapter 5                              |      |     |     |     |     |     |     |     |     |     |     |     |
| Chapter 6                              |      |     |     |     |     |     |     |     |     |     |     |     |

|                                        | 2021 |     |     |     |     |     |     |     |     |     |     |     |
|----------------------------------------|------|-----|-----|-----|-----|-----|-----|-----|-----|-----|-----|-----|
|                                        | Jan  | Feb | Mar | Apr | May | Jun | Jul | Aug | Sep | Oct | Nov | Dec |
| Proposal Preparation                   |      |     |     |     |     |     |     |     |     |     |     |     |
| Proposal Presentation                  |      |     |     |     |     |     |     |     |     |     |     |     |
| Application of Ethics Approval         | √    | √   |     |     |     |     |     |     |     |     |     |     |
| Participants Recruitment and Selection |      |     | √   | √   | √   | √   | √   | √   | √   | √   | √   | √   |
| Intervention Implementation            |      |     | √   | √   | √   | √   | √   | √   | √   | √   | √   | √   |
| Data Collection                        |      |     | √   | √   | √   | √   | √   | √   | √   | √   | √   | √   |
| Data Analysis                          |      |     |     |     |     |     |     |     |     |     |     |     |
| Chapter 1                              | √    | √   | √   | √   | √   | √   | √   | √   | √   | √   | √   | √   |
| Chapter 2                              | √    | √   | √   | √   | √   | √   | √   | √   | √   | √   | √   | √   |
| Chapter 3                              | √    | √   | √   | √   | √   | √   | √   | √   | √   | √   | √   | √   |
| Chapter 4                              |      |     |     |     |     |     |     |     |     |     |     |     |
| Chapter 5                              |      |     |     |     |     |     |     |     |     |     |     |     |
| Chapter 6                              |      |     |     |     |     |     |     |     |     |     |     |     |

|                                        | 2022 |     |     |     |     |     |     |     |     |     |     |     |
|----------------------------------------|------|-----|-----|-----|-----|-----|-----|-----|-----|-----|-----|-----|
|                                        | Jan  | Feb | Mar | Apr | May | Jun | Jul | Aug | Sep | Oct | Nov | Dec |
| Proposal Preparation                   |      |     |     |     |     |     |     |     |     |     |     |     |
| Proposal Presentation                  |      |     |     |     |     |     |     |     |     |     |     |     |
| Application of Ethics Approval         |      |     |     |     |     |     |     |     |     |     |     |     |
| Participants Recruitment and Selection | √    | √   | √   | √   | √   | √   | √   | √   | √   | √   | √   | √   |
| Intervention Implementation            | √    | √   | √   | √   | √   | √   | √   | √   | √   | √   | √   | √   |
| Data Collection                        | √    | √   | √   | √   | √   | √   | √   | √   | √   | √   | √   | √   |
| Data Analysis                          |      |     |     |     |     |     |     |     | √   | √   | √   | √   |
| Chapter 1                              | √    | √   | √   | √   | √   | √   | √   | √   | √   | √   | √   | √   |
| Chapter 2                              | √    | √   | √   | √   | √   | √   | √   | √   | √   | √   | √   | √   |
| Chapter 3                              | √    | √   | √   | √   | √   | √   | √   | √   | √   | √   | √   | √   |
| Chapter 4                              |      |     |     |     |     |     |     |     |     |     |     |     |
| Chapter 5                              |      |     |     |     |     |     |     |     |     |     |     |     |
| Chapter 6                              |      |     |     |     |     |     |     |     |     |     |     |     |

|                                        | 2023 |     |     |     |     |     |     |     |     |     |     |     |
|----------------------------------------|------|-----|-----|-----|-----|-----|-----|-----|-----|-----|-----|-----|
|                                        | Jan  | Feb | Mar | Apr | May | Jun | Jul | Aug | Sep | Oct | Nov | Dec |
| Proposal Preparation                   |      |     |     |     |     |     |     |     |     |     |     |     |
| Proposal Presentation                  |      |     |     |     |     |     |     |     |     |     |     |     |
| Application of Ethics Approval         |      |     |     |     |     |     |     |     |     |     |     |     |
| Participants Recruitment and Selection | √    | √   | √   | √   | √   | √   | √   | √   | √   | √   | √   | √   |
| Intervention Implementation            | √    | √   | √   | √   | √   | √   | √   | √   | √   | √   | √   | √   |
| Data Collection                        | √    | √   | √   | √   | √   | √   | √   | √   | √   | √   | √   | √   |
| Data Analysis                          | √    | √   | √   | √   | √   | √   | √   | √   | √   | √   | √   | √   |
| Chapter 1                              | √    | √   | √   | √   | √   | √   | √   | √   | √   | √   | √   | √   |
| Chapter 2                              | √    | √   | √   | √   | √   | √   | √   | √   | √   | √   | √   | √   |
| Chapter 3                              | √    | √   | √   | √   | √   | √   | √   | √   | √   | √   | √   | √   |
| Chapter 4                              | √    | √   | √   | √   | √   | √   | √   | √   | √   | √   | √   | √   |
| Chapter 5                              | √    | √   | √   | √   | √   | √   | √   | √   | √   | √   | √   | √   |
| Chapter 6                              | √    | √   | √   | √   | √   | √   | √   | √   | √   | √   | √   | √   |

|                                        | 2024 |     |     |     |     |     |     |     |     |     |     |     |
|----------------------------------------|------|-----|-----|-----|-----|-----|-----|-----|-----|-----|-----|-----|
|                                        | Jan  | Feb | Mar | Apr | May | Jun | Jul | Aug | Sep | Oct | Nov | Dec |
| Proposal Preparation                   |      |     |     |     |     |     |     |     |     |     |     |     |
| Proposal Presentation                  |      |     |     |     |     |     |     |     |     |     |     |     |
| Application of Ethics Approval         |      |     |     |     |     |     |     |     |     |     |     |     |
| Participants Recruitment and Selection | √    | √   | √   | √   | √   | √   | √   | √   | √   | √   | √   | √   |
| Intervention Implementation            | √    | √   | √   | √   | √   | √   | √   | √   | √   | √   | √   | √   |
| Data Collection                        | √    | √   | √   | √   | √   | √   | √   | √   | √   | √   | √   | √   |
| Data Analysis                          | √    | √   | √   | √   | √   | √   | √   | √   | √   | √   | √   | √   |
| Chapter 1                              | √    | √   | √   | √   | √   | √   | √   | √   | √   | √   | √   | √   |
| Chapter 2                              | √    | √   | √   | √   | √   | √   | √   | √   | √   | √   | √   | √   |
| Chapter 3                              | √    | √   | √   | √   | √   | √   | √   | √   | √   | √   | √   | √   |
| Chapter 4                              | √    | √   | √   | √   | √   | √   | √   | √   | √   | √   | √   | √   |
| Chapter 5                              | √    | √   | √   | √   | √   | √   | √   | √   | √   | √   | √   | √   |
| Chapter 6                              | √    | √   | √   | √   | √   | √   | √   | √   | √   | √   | √   | √   |

|                                        | 2025 |     |     |     |     |     |     |     |     |     |     |     |
|----------------------------------------|------|-----|-----|-----|-----|-----|-----|-----|-----|-----|-----|-----|
|                                        | Jan  | Feb | Mar | Apr | May | Jun | Jul | Aug | Sep | Oct | Nov | Dec |
| Proposal Preparation                   |      |     |     |     |     |     |     |     |     |     |     |     |
| Proposal Presentation                  |      |     |     |     |     |     |     |     |     |     |     |     |
| Application of Ethics Approval         |      |     |     |     |     |     |     |     |     |     |     |     |
| Participants Recruitment and Selection | √    | √   | √   | √   | √   | √   |     |     |     |     |     |     |
| Intervention Implementation            | √    | √   | √   | √   | √   | √   |     |     |     |     |     |     |
| Data Collection                        | √    | √   | √   | √   | √   | √   |     |     |     |     |     |     |
| Data Analysis                          | √    | √   | √   | √   | √   | √   |     |     |     |     |     |     |
| Chapter 1                              | √    | √   | √   | √   | √   | √   |     |     |     |     |     |     |
| Chapter 2                              | √    | √   | √   | √   | √   | √   |     |     |     |     |     |     |
| Chapter 3                              | √    | √   | √   | √   | √   | √   |     |     |     |     |     |     |
| Chapter 4                              | √    | √   | √   | √   | √   | √   |     |     |     |     |     |     |
| Chapter 5                              | √    | √   | √   | √   | √   | √   |     |     |     |     |     |     |
| Chapter 6                              | √    | √   | √   | √   | √   | √   |     |     |     |     |     |     |

